## Abstract

**Background:**

Cancer-related fatigue is one of the most prevalent, prolonged and distressing side effects of prostate cancer treatment with androgen deprivation therapy. Preliminary evidence suggests natural therapies such as nutrition therapy and structured exercise prescription can reduce symptoms of cancer-related fatigue. Men appear to change their habitual dietary patterns after prostate cancer diagnosis, yet prostate-specific dietary guidelines provide limited support for managing adverse side effects of treatment. The exercise literature has shown high intensity interval training can improve various aspects of health that are typically impaired with androgen deprivation therapy; however exercise at this intensity is yet to be conducted in men with prostate cancer. The purpose of this study is to examine the effects of nutrition therapy beyond the current healthy eating guidelines with high intensity interval training for managing cancer-related fatigue in men with prostate cancer treated with androgen deprivation therapy.

**Methods/design:**

This is a two-arm randomized control trial of 116 men with prostate cancer and survivors treated with androgen deprivation therapy. Participants will be randomized to either the intervention group i.e. nutrition therapy and high intensity interval training, or usual care. The intervention group will receive 20 weeks of individualized nutrition therapy from an Accredited Practising Dietitian, and high intensity interval training (from weeks 12–20 of the intervention) from an Accredited Exercise Physiologist. The usual care group will maintain their standard treatment regimen over the 20 weeks. Both groups will undertake primary and secondary outcome testing at baseline, week 8, 12, and 20; testing includes questionnaires of fatigue and quality of life, objective measures of body composition, muscular strength, cardiorespiratory fitness, biomarkers for disease progression, as well as dietary analysis. The primary outcomes for this trial are measures of fatigue and quality of life.

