We hypothesized that 12-weeks of nutrition therapy, compared to 12 weeks of usual care, will improve CRF and quality of life in men with prostate cancer treated with ADT. It is further hypothesized a 20-week nutrition therapy intervention with 8 weeks of high intensity interval training, compared to 20 weeks of usual care, will improve CRF and quality of life in men with prostate cancer treated with ADT. Secondary measures of body composition, functional capacity, metabolic syndrome and biomarkers such as prostate specific antigen, insulin like growth factor [43]-1, IGF-2, IGF binding protein-3, interleukin [IL]-6, and IL-8), will be measured and analyzed between and within groups. We hypothesis nutrition therapy alone, and with high intensity exercise will improve body composition, functional capacity, and biomarkers of metabolic syndrome and prostate cancer progression.

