### Measurements

All measurements for primary and secondary outcomes will take place at baseline, week 8, week 12, and week 20 (see Table 1). A familiarization trial including the functional capacity and peak aerobic power (V̇O_2peak_) tests will take place at least 7 days prior to baseline testing. Participants will be asked to refrain from vigorous exercise, caffeine, alcohol, food and beverages (except for water) for 12 h before all testing sessions.

**Table 1 Tab1:** Data collection schedule

Assessments	Time (weeks)				
	Baseline^a^		Week 8	Week 12	Week 20
Screening					
Participant eligibility	✓	Randomization			
Adult Pre-exercise Screening System	✓				
Medical history form and medications	✓				
Primary outcomes					
Function Assessment of Cancer Therapy-Fatigue	✓	Randomization	✓	✓	✓
European Organization of Research and Treatment of Cancer QLQ-C30*	✓		✓	✓	✓
European Organization of Research and Treatment of Cancer QLQ-PR25^□^	✓		✓	✓	✓
The Medical Outcomes Study 36-Item Short-Form 36	✓		✓	✓	✓
Second Outcomes					
Anthropometric physique traits	✓	Randomization	✓	✓	✓
Body composition^b^	✓		✓	✓	✓
Isometric strength	✓		✓	✓	✓
Chest and leg one repetition maximum test	✓		✓	✓	✓
Sit to stand test	✓		✓	✓	✓
Six-meter walk test	✓		✓	✓	✓
400-meter walk test	✓		✓	✓	✓
Cardiorespiratory fitness^c^	✓		✓	✓	✓
Blood collection	✓		✓	✓	✓
Wollongong Dietary Inventory	✓		✓	✓	✓
24-h diet recall^d^	✓		✓	✓	✓
Depression Anxiety Stress Scale	✓		✓	✓	✓
Insomnia Severity Index	✓		✓	✓	✓
Physical Activity Enjoyment Scale	✓		✓	✓	✓
Godin Leisure-Time Physical Activity Questionnaire	✓		✓	✓	✓
Accelerometer^e,f^	✓		✓	✓	✓

^a^Nutrition and exercise intervention commences Week 0 after randomisation

^b^Dual energy X-ray absorptiometry

^c^V̇O_2peak_ test

^d^Conducted every 2 weeks

^e^Actigraph GT3X+

^f^to be worn for 7 consecutive days

*Cancer quality of life questionnaire for people with cancer

^□^Cancer quality of life questionnaire for people with prostate cancer

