### Primary outcomes

#### Fatigue

Fatigue will be measured using The Functional Assessment of Cancer Therapy: Fatigue (FACT-F) questionnaire, which reports weekly fatigue on a scale of 0–52, with higher values indicating less fatigue [45]. The FACT-F has shown good reliability and validity (Cronbach’s α: 0.93-0.94) for predicting clinically significant treatment outcomes of CRF [46].

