#### Cancer-specific quality of life

The European Organization for Research and Treatment of Cancer (EORTC) QLQ-C30 is a 30 item cancer-specific instrument including the following domains; physical, role, emotional, social, and cognitive, global quality of life, fatigue, pain, and emesis. The EORTC QLQ-C30 has shown a high reliability (Cronbach’s α; 0.63-.80) in cancer patients [47].

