#### Prostate cancer-specific quality of life

The EORTC QLQ–PR25 is a 25 question prostate cancer-specific instrument including domains; urinary, bowel, use of incontinence aids, treatment-related symptoms, sexual activity and sexual function [48]. The EORTC QLQ – PR25 questionnaire has shown good internal reliability (Cronbach’s α; 0.70-0.86) for prostate specific treatment-related side effects [49].

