#### General health and well-being

The Medical Outcomes Study 36-Item Short-Form 36 Health Survey (SF-36) is scored by eight scales encompassing physical and mental measures [50]. The SF-36 questionnaire has widely been used to measure general health and well-being, with good construct validity (Cronbach’s α; > 0.85) in cancer patients [51].

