### Sample Size Calculation

Sample size calculations were complete using Vanderbilt Power and Sample Size software (Vanderbilt University, TN). Combined diet and exercise interventions with CRF as an outcome are relatively limited. A diet and exercise intervention in men treated with ADT showed prostate cancer-specific CRF (as measured by FACT-F) scores improved by 3.7 – 14.2 (CI, 95%; adjusted mean 8.9 points) in the intervention group compared to the control group [20]. Assuming FACT-F scores for this group were normally distributed with a SD of 8.9, a true difference between the experimental and control arms of 5.2, and a power of 0.8, we would need 47 experimental and control participants to be able to reject the null hypothesis. The type 1 error probability associated with this test of the null hypothesis is 0.05. With an anticipated 20% attrition rate based on previous research from our laboratory, we would need 58 experimental and control group participants to be able to reject the null hypothesis.

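### Four questionnaires are primary for two hypotheses, but the 0.05, the 0.8 power and the 47 per arm cover one FACT-F comparison at an unnamed week

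*Protocol article*

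**What the plan says.** **Primary set.** The abstract (Methods/design) puts it in the plural: "The primary outcomes for this trial are measures of fatigue and quality of life". Table 1 lists four instruments under primary outcomes, the last being "The Medical Outcomes Study 36-Item Short-Form 36". The Primary outcomes section describes them:

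- FACT-F: a single score, "which reports weekly fatigue on a scale of 0–52, with higher values indicating less fatigue".
- QLQ-C30: nine listed domains, "physical, role, emotional, social, and cognitive, global quality of life, fatigue, pain, and emesis". Fatigue is among them, so it is measured twice within the primary set.
- QLQ-PR25: six listed domains, "urinary, bowel, use of incontinence aids, treatment-related symptoms, sexual activity and sexual function".
- SF-36: "is scored by eight scales encompassing physical and mental measures".

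No domain of the last three is singled out, and no instrument is called the lead.

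**Hypotheses.** The Background states two. The first is for week 12: "We hypothesized that 12-weeks of nutrition therapy, compared to 12 weeks of usual care, will improve CRF and quality of life". The second makes the same claim for the combined diet and exercise programme against usual care at week 20.

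**Sample size.** The Sample Size Calculation uses FACT-F only: true difference 5.2, SD 8.9, power 0.8, 47 per arm, and 58 per arm after 20% attrition. It continues: "The type 1 error probability associated with this test of the null hypothesis is 0.05". It does not say which week this test refers to.

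**The concern.** Which outcomes are primary is settled in the protocol. Here it is settled as four instruments of equal rank, for two hypotheses, next to an error rate and a sample size that describe one test on one of them. The two parts cannot both describe the confirmatory analysis.

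The stated figures are affected whichever way success is read. If one positive instrument at one week is enough, 0.05 is not the error rate of the primary claim. If fatigue and quality of life must both improve, 0.8 is not its power. The Discussion wants the results to support clinical guidelines, so it matters that a reader can tell beforehand which result would make the trial positive.

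**Working it through.** **Inputs from the document.** Difference 5.2, SD 8.9, alpha 0.05, power 0.8 and 20% attrition (Sample Size Calculation); 1:1 allocation (Randomisation); four primary instruments (Table 1); two hypotheses (Background). Correlations between test statistics are not given. They are assumptions here, so a range is shown.

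**1. Reproduce the plan's figure.** Two-sample t test, two-sided 0.05:

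- Normal approximation: n = 2 × [8.9 × (1.960 + 0.842) / 5.2]² = 45.98, so 46 per arm.
- Noncentral t: at n = 47 the noncentrality is 5.2 / (8.9 × √(2/47)) = 2.83 on 92 df, and power is 0.800. So 47 per arm is reproduced.
- One-sided 0.05 gives 37 per arm by the normal approximation and does not match.
- Attrition: 47 / 0.8 = 58.75, against 58 stated. This is a rounding matter and not the point here.

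The calculation therefore covers exactly one two-sided FACT-F comparison.

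**2. Count the declared family.** 4 instruments × 2 weeks = 8 tests, taking one test per instrument per week.

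**3. Reading A: any one success counts.** With independent tests the chance of at least one false positive is 1 − 0.95⁸ = 0.337 two-sided, and 1 − 0.975⁸ = 0.183 counting only the favourable direction. With equally correlated normal test statistics and no true effect:

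| Assumed correlation | Two-sided at 0.05 | Favourable direction only (nominal 2.5%) |
|---|---|---|
| 0 | 33.7% | 18.3% |
| 0.3 | 30.0% | 15.2% |
| 0.5 | 25.0% | 12.5% |
| 0.7 | 19.1% | 9.5% |
| 0.9 | 11.9% | 6.0% |

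Letting the correlation between instruments (0.3 to 0.7) differ from that between weeks (0.5 to 0.8) gives 20% to 30% two-sided and 10% to 15% in the favourable direction.

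**4. Reading A with the error rate restored by an equal (Bonferroni) split**, keeping 5.2 and 8.9 as the standardised effect:

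| Tests | Alpha each | Power at 47 per arm | n per arm for 0.8 | With 20% attrition |
|---|---|---|---|---|
| 1 | 0.05 | 80% | 47 | 59 |
| 2 | 0.025 | 71% | 57 | 72 |
| 4 | 0.0125 | 61% | 67 | 84 |
| 8 | 0.00625 | 52% | 77 | 97 |

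A later alpha split would therefore leave the stated sample size too small.

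**5. Reading B: fatigue and quality of life must both succeed.** The error rate is not inflated. Suppose one quality-of-life score has the same standardised effect as FACT-F, so that each test has power 0.8. Joint power is then 0.8 × 0.8 = 0.64 if the tests are independent, 0.69 at correlation 0.5 and 0.75 at 0.9. It reaches 0.8 only at perfect correlation.

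**The case against.** **The inflation is conditional.** The document nowhere says that one significant instrument makes the trial positive. Its aims and hypotheses join fatigue and quality of life with *and*. A reader might infer that the false positive rate certainly exceeds 5%; the text does not establish that. This stands, and it is why both readings are worked out. It does not remove the mismatch, because under the joint reading it is the stated power that fails.

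**Counting every domain.** The listed domains add up to 1 + 9 + 6 + 8 = 24 scores, or 48 over two weeks, and a reader might infer a false positive chance near 1 − 0.95⁴⁸ = 91%. The document does not support that. It names instruments as primary and lists domains as description, the scales are correlated, and which score of each instrument is analysed can be left to the analysis plan. The supportable family is 8 tests.

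**An unseen analysis plan may adjust.** It may, so the absence of a multiplicity procedure is not the finding. The finding is what this document fixes: a plural primary set beside a one-test alpha and sample size.

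**FACT-F is visibly the lead.** The stated purpose is managing fatigue, FACT-F is listed first, and only FACT-F is powered. That makes it the natural choice, but nothing designates it, and Table 1 ranks all four equally. A reader might also infer that the sample size refers to week 20. It names no week, and week 12 is the first aim.

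**Conclusion.** The point holds as a mismatch between the declared primary set and the test behind the error rate, power and sample size. Four instruments at two weeks are primary, while one FACT-F comparison at an unstated week is sized.

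If any success counts, the false positive chance is about 12% to 34% two-sided, or about 6% to 12.5% in the favourable direction at correlations 0.9 to 0.5. If both domains must succeed, error is controlled but power for the joint claim is below 0.8 unless the endpoints are perfectly correlated. These sizes rest on one test per instrument per week, on assumed correlations and, for the joint-power figures, on equal standardised effects. The mismatch itself rests on none of these; it can be read directly from the document.

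**What to change.** Before outcome data are seen:

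1. Name one primary outcome: the difference between arms in FACT-F, the outcome the sample size uses, at one stated week.
2. The sponsor chooses and states the leading week. Week 20 tests the full intervention; week 12 is the first aim. The sample size does not decide between them.
3. Test FACT-F at the other week next, in fixed sequence at two-sided 0.05, and only if the first test succeeds. If wanted, follow with one named quality-of-life score.
4. Make all remaining questionnaire scores secondary, reported with confidence intervals and without confirmatory claims.
5. State in the Sample Size Calculation which week the 5.2-point difference refers to.

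This leaves 0.05 and 47 per arm unchanged, so it costs wording in the protocol and the registration. The downside is real: the aims give quality of life equal standing with fatigue, and it would lose that status, with fewer scales able to carry a confirmatory claim. If equal standing must be kept, the alternatives are an alpha split or a stated rule that both must succeed, each with the sample size recalculated.

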**Discussion:**

This study is the first of its kind to determine the efficacy of nutrition therapy above the healthy eating guidelines and high intensity interval training for alleviating prostate-cancer related fatigue. If successful, nutrition therapy and high intensity interval training may be proposed as an effective therapy for managing cancer-related fatigue and improving quality of life in men during and after prostate cancer treatment.

**Trial registration:**

Australian New Zealand Clinical Trials Registry ACTRN12615000512527. Trial registered on the 22/5/2015.

## Background

Prostate cancer has become the most significant major malignancy of men, severely impacting disease-specific morbidity and mortality [1–3]. Advances in treatment of the disease, particularly through the use of Androgen Deprivation Therapy (ADT; a primary and mainstay treatment of prostate cancer), has seen prostate cancer 5-year survival rate increase to 92% [2]. Despite ADT’s efficacy in disease control, the physiological alterations resulting from ADT have profound adverse effects, including increased fatigue [4, 5], metabolic risk [6–8], cardiovascular risk [6, 9], change in body composition (increased fat mass and decreased muscle mass) [10, 11], and reduced functional capacity [12]; the amalgamation of these side effects severely reduces quality of life [13–15]. Cancer-related fatigue (CRF) is a distressing, persistent, subjective sense of physical, emotional and/or cognitive tiredness or exhaustion related to cancer or cancer treatment that is not proportional to recent activity and interferes with usual functioning [16]. CRF is the most common adverse effect of ADT, with up to 74% of men treated with ADT experiencing symptoms of CRF [4]. Incidence of CRF can be seen as early as 12 weeks after treatment initiation, and may last for longer than 12 months post-treatment in men treated with ADT [4, 5, 17]. Given the widespread use of ADT in managing prostate cancer progression, many men are living with ADT-related side effects during the course of treatment, and longer into prostate cancer survivorship. Current management strategies of CRF are predominantly through pharmacological therapy [16, 18]; yet more recently, natural therapies such as diet and exercise have demonstrated clinically significant reductions of CRF symptoms in men with prostate cancer treated with ADT [19, 20].

The benefits of aerobic exercise (performed at 65–80% age predicted maximum heart rate [APMHR] three times per week) and progressive resistance training (8–12 exercises, 2–4 sets of 8–12 repetitions performed 2–3 times per week) in isolation, or when prescribed together, are well established for improving CRF in men with prostate cancer [21–25]. Recently, there has been particular interest in the use of high intensity interval training [85–95% peak heart rate (HR_peak_) interspersed with period of active recovery] for improving CRF, body composition, and quality of life in oncological populations for managing treatment-related side effects [26–28]. In colorectal cancer survivors, 12 supervised high intensity interval training sessions (4x4 min bouts of cycling at 85–95% HR_peak_, interspersed with 3 min of active recovery at 50–70% HR_peak_) performed over 4 weeks showed greater improvements in cardiorespiratory fitness and total body mass, when compared to 12 supervised moderate intensity exercise sessions (50 min of cycling at 50-70% HR_peak_) [29]. Thus, high intensity interval training may provide an optimal exercise prescription for improving various aspects of health that are typically impaired with ADT; however exercise at this intensity is yet to be conducted in men with prostate cancer.

Combined nutrition therapy and exercise prescription has the potential to optimize management for CRF and other ADT related side effects. Aerobic exercise (55–80% APMHR) performed 2-3 times per week for 12-weeks, with healthy eating group based seminars every 2 weeks, has demonstrated clinically significant improvements in CRF and quality of life in sedentary men treated with ADT [19, 20]. In contrast individual nutrition advice to meet the United Kingdom Dietary guidelines [30] with 30 min per day of brisk walking for 24 weeks demonstrated no significant changes in CRF or quality of life compared to usual care [31]. Thus it appears CRF may be better managed with structured exercise prescription and concurrent healthy eating. Whilst Bourke and colleagues [19, 20] demonstrated significant improvements in CRF, the nutrition consults were group-based, which fails to consider individual dietary requirements and is not representative of standard dietetic practice. Thus the effects of tailored nutrition therapy beyond the healthy eating guidelines, with adjunctive structured exercise prescription on the burden of CRF remains to be elucidated.

Dietary manipulation has been identified to be an important lifestyle factor to alleviate ADT related side effects [32–34]; yet the efficacy of dietary interventions in isolation during treatment or into prostate cancer survivorship are limited for supporting the adverse side effects seen from ADT. Importantly, prostate cancer-specific dietary guidelines provide limited support and guidance for alleviating adverse treatment-related side effects, including CRF [35, 36]. In non-oncological populations, structured individualized nutrition therapy by an Accredited Practising Dietitian is recommended for adults who are overweight, obese, insulin resistant, and have altered lipid and triglyceride metabolism [37–39]; all notable adverse side effects from ADT. Yet the translation of this nutrition therapy in prostate cancer is yet to be elucidated. Recently, a Mediterranean-style diet pattern has been shown to improve metabolic and cardiovascular parameters in men at risk of prostate cancer [40]. Adherence to an anti-inflammatory properties of a Mediterranean diet have shown small reductions in hypertension (reduced systolic blood pressure; SE = – 1.44mm Hg [95% CI, -2.88 – 0.01]; and diastolic blood pressure; SE = -0.70mm Hg [95% CI, -1.34 – 0.07) [41], and risk of type 2 diabetes (RR = 0.93; 95% CI, 0.89 – 0.98) [42]; thus showing plausible metabolic and cardiovascular effects on known ADT related side effects. Yet practical application of the Mediterranean-style diet pattern to men treated with ADT for management of CRF and improving quality of life is yet to be ellucidated.

Literature to date has encompassed general healthy eating guidelines for the management of prostate cancer treated related side effects [19, 20, 31], however general guidelines do not take into account the specific dietary requirements needed to manage the ADT-related side effects. Therefore, the role of specific individualized nutrition therapy tailored to alleviate the side effects of ADT, particularly CRF, and improve quality of life warrants investigation.

This study aims to:Investigate whether 12-weeks of nutrition therapy, compared to 12 weeks of usual care, can improve prostate CRF and quality of life in men treated with ADT.Assess the combined benefits of 20-weeks of nutrition therapy with 8-weeks of high intensity exercise (weeks 12–20), compared to 20 weeks of usual care, on CRF and quality of life in men treated with ADT.

We hypothesized that 12-weeks of nutrition therapy, compared to 12 weeks of usual care, will improve CRF and quality of life in men with prostate cancer treated with ADT. It is further hypothesized a 20-week nutrition therapy intervention with 8 weeks of high intensity interval training, compared to 20 weeks of usual care, will improve CRF and quality of life in men with prostate cancer treated with ADT. Secondary measures of body composition, functional capacity, metabolic syndrome and biomarkers such as prostate specific antigen, insulin like growth factor [43]-1, IGF-2, IGF binding protein-3, interleukin [IL]-6, and IL-8), will be measured and analyzed between and within groups. We hypothesis nutrition therapy alone, and with high intensity exercise will improve body composition, functional capacity, and biomarkers of metabolic syndrome and prostate cancer progression.

